## Abstract

**Background:**

Nearly 11% of the European population is affected by energy poverty. Energy poverty is defined by the European Commission (2016) as the inability to afford basic energy services to guarantee a decent standard of living. Energy poverty is considered a complex, multidimensional problem that affects environment, housing, urban development, and health. Living in energy poverty conditions is associated with poorer human health and wellbeing. Hence, the WELLBASED intervention programme aims to design, implement and evaluate a comprehensive urban programme, based on the social-ecological model, to reduce energy poverty and its effects on the citizens’ health and wellbeing in six European urban study sites: Valencia, Spain; Heerlen, The Netherlands; Leeds, United Kingdom; Edirne, Turkey; Obuda, Hungary, and; Jelgava, Latvia.

**Methods:**

A controlled trial is performed. A total of 875 participants are recruited (125–177 per study site) to receive the WELLBASED intervention programme for 12 months (intervention condition) and 875 participants act as controls (control condition). Data will be collected with a baseline measurement at inclusion (T0), and follow-up measurements after 6 months (T1), 12 months (T2), and 18 months (T3). In both study arms, effects of the WELLBASED intervention programme are measured: health-related quality of life (HR-QoL), mental health, frailty in older adults, self-perceived health, chronic conditions, and care utilization. At the same time points, household expenditure on energy and energy consumption are obtained. In the intervention arm, health-monitoring data (i.e. peak flow, oxygen saturation, blood pressure, and heart rate) are obtained monthly and sleep quality with a three-month interval. Household data with regard to temperature, humidity and air quality are collected near real-time by home sensors. Qualitative interviews are conducted in each study site to evaluate the impacts of the WELLBASED intervention programme and to help explain findings.

**Discussion:**

The WELLBASED intervention programme will provide new insights into the effectiveness of a comprehensive urban programme to tackle energy poverty and its effects on health and wellbeing across Europe. Hence, this study can contribute to European-wide replicable solutions for policy-makers and city practitioners to alleviate energy poverty.

**Trial registration:**

ISRCTN registry number is ISRCTN14905838. Date of registration is 15/02/2022.

**Supplementary Information:**

The online version contains supplementary material available at 10.1186/s12889-022-13968-2.

## Background

Energy poverty has become a major societal challenge that is estimated to affect nearly 11% of the European population [1, 2]. Due to rising energy prices, low incomes and poor energy efficiency of housing, around 54 million Europeans are not able to adequately heat their homes at an affordable cost [3, 4]. Energy poverty is defined by the European Commission (2016) as ‘’the inability to afford basic energy services (heating, cooling, lighting, mobility and power) to guarantee a decent standard of living due to a combination of low income, high energy expenditure and low energy efficiency of homes’’ [5]. It is most likely to occur in urban areas with high unemployment and poverty along with poor quality buildings or poor built environment [3].

A growing evidence base highlights the negative impact of living in energy poor conditions on human health and wellbeing [6–11]. For example, a survey among 536 United Kingdom social housing residents reported that the inability to keep a households’ living room warm together with concerns about the affordability of energy bills, was associated with lower satisfaction with life [9]. Residing in cold homes has been associated with poorer mental health, cardiovascular and respiratory diseases and minor illnesses such as cold and flu [9–12]. Those with chronic and severe illnesses, including disabilities, and older people seem to be worst affected [13–15]. This is explained by the fact that sedentary or ill people are less able to generate their own heat, spend more time inside their homes, and are more likely to be on low incomes and thus unable to afford adequate energy [11, 16, 17].

Interventions to reduce energy poverty and mitigate its effects on health and wellbeing are needed. Thus far, the majority of studies reporting on interventions to reduce energy poverty focus on one specific intervention strategy; [6, 18–21]. that is the implementation of housing improvement measures [6, 19–21]. Although, the improvement of housing, e.g. thermal comfort in the home, can lead to health improvements [19], a more comprehensive intervention approach seems warranted [22, 23]. Such an approach may be guided by the social-ecological model, which maps the interactions between the individual, the community, and the physical, social, and political environments that affect health and wellbeing [24]. The purpose of this paper is to describe the evaluation framework for the WELLBASED intervention programme: a comprehensive, urban programme to improve health and wellbeing by tackling energy poverty.

### WELLBASED

The WELLBASED project will design, implement and evaluate a comprehensive urban programme, based on the social-ecological model, to reduce energy poverty and its effects on the citizens health and wellbeing. Six urban study sites in Europe (Valencia, Spain; Heerlen, The Netherlands; Leeds, United Kingdom; Edirne, Turkey; Obuda, Hungary, and Jelgava, Latvia) will implement the WELLBASED intervention programme. The WELLBASED study cities represent not only different urban realities but also a diverse range of welfare and healthcare models. The WELLBASED project was established in response to the HORIZON 2020 call “Innovative actions for improving urban health and wellbeing- addressing environment, climate and socioeconomic factors’’, funded under GA 945,097.

### Objectives

The aim of this study is to evaluate the WELLBASED intervention programme, using a controlled trial design. The short, and mid-term effects of the programme on energy poverty and health and wellbeing indicators are evaluated in comparison to a control condition (i.e. no specific programme to address energy poverty is applied). Cost-effectiveness of the intervention programme is assessed. Furthermore, differential impact of the intervention programme with regard to gender and social determinants is explored. Additionally, interviews and focus groups are implemented in each study site to evaluate the impact of the intervention programme and to help explain outcomes. To this end, the controlled trial design is combined with a qualitative approach that offers explanations of the impact and implementation of the WELLBASED intervention programme.

### Hypothesis

The hypothesis of this study is that vulnerable people living in energy poverty who participate in the WELLBASED intervention programme have more favourable results with regard to indicators of energy poverty, health and wellbeing in comparison to the people participating in the control condition.

## Methods

This study protocol adhered to the SPIRIT guidelines for clinical trial protocols [25].

### Study design

A controlled trial is performed with an intervention condition and a control condition (i.e. no specific programme to address energy poverty is applied) in six study sites in Europe. Measures are taken at baseline (T0), at 6 months (T1), at 12 months (T2) and 18 months after baseline (follow-up; T3) in both research groups. In addition, in the intervention condition additional frequent monitoring of health and housing conditions takes place. Moreover, qualitative interviews with a subsample of participants undergoing the intervention condition take place near the beginning of the intervention (3–6 months) and after termination of the intervention (15–18 months).

The WELLBASED intervention programme targets adults ≥ 18y in vulnerable situations, living in energy poverty conditions that belong to one of the study sites. An overview of study sites and the target population is presented in Table 1. Local organisations (e.g. the social services department or an non-governmental organisation (NGO) that supports vulnerable groups) or the local research team, depending on study site, select eligible individuals. Recruitment of study participants and baseline data collection is scheduled to commence in autumn 2022. Potential participants in the catchment area of an intervention or control site receive information about the study and an invitation to provide informed consent to join the study by the study site team. Generally, in each selected household, the person who is considered responsible for the accommodation or best placed to provide the information is invited to join the study and to complete questionnaires. This participant is also invited to participate in health data collection and, when applicable, to join qualitative interviews at a later stage. In some cases more than one person per household may be invited to join the study. Participants only join the study after they have provided informed consent. Study participants, intervention providers and research assistants are not blinded due to the nature of the intervention. The study is performed in accordance with the capacity, organizational and contextual factors of each of the six participating cities, as described below.

**Table 1 Tab1:** Study site characteristics

STUDY SITE	RECRUITMENT OF PARTICIPANTS	
	**TARGET GROUP**	**NUMBER OF PARTICIPANTS**
VALENCIA (SPAIN)	Three districts with high sociodemographic vulnerability, due to an aged population, lower incomes than the city average and higher percentages of people at risk of poverty	177 participants per study arm
HEERLEN (THE NETHERLANDS)	Social housing tenants from two districts in the northern part of the city with low incomes, high energy bills, low energy measures and bad housing conditions	156 participants per study arm
EDIRNE (TURKEY)	Low-income households in five neighbourhoods, where vulnerable groups, including Roma, are highly represented	125 participants per study arm
JELGAVA (LATVIA)	The most vulnerable households, described by low income levels, long-term unemployment (> 1 year), disabled people, poor housing quality, single-parent families, pensioners (especially suffering loneliness), and provided by the municipality	146 participants per study arm
LEEDS (United Kingdom)	Social housing tenants, managed by the City Council, with poor housing quality, classified as energy efficiency band D or below. Target group has different vulnerabilities: low income, older people, disabled people, single parents and recent migrants	125 participants per study arm
OBUDA (HUNGARY)	Vulnerable inhabitants of Óbuda-Békásmegyer, the 3^rd^ district of Budapest, characterised by low incomes, victims of domestic violence and/or drug abuse, households with disabled and/or chronically ill members, unemployed members, and single mothers	146 participants per study arm

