### Study population and eligibility to participate in the study

All participants who provide informed consent are enrolled in the study. We aim to include 1750 participants in total. Each study site allocates at least 125 participants to the intervention condition and 125 participants to the control condition. Detailed numbers of participants per study site are presented in Table 1. Study sites might apply randomization at individual or cluster level to create intervention and control condition.

Study participants are included if they: (i) are aged ≥ 18 years old, (ii) are in a vulnerable situation (e.g. unemployed, low income, single parents, parents with dependent children, seniors (65 +) with dependency conditions, seniors (65 +) living alone, people with disabilities attended by social services, belonging to a minority, migrant situation), (iii) living in energy poverty conditions, and (vi) belonging to the recruitment sites identified by the local partners for the study. The research assistant recruits potential participants in collaboration with local agencies that work in the catchment area. Together they determine energy poverty conditions (criterion iii), based on their knowledge of and experience with the target population. The primary indicators suggested by EU Energy Poverty Observatory (EPOV) are used as guideline to assess the energy poverty status. EPOV established the following criteria:i.arrears on utility bills;ii.low absolute energy expenditure (below half of the national median (M/2));iii.high share of energy expenditure in income (double of the national median share of energy expenditure in income (2 M)) andiv.inability to keep home adequately warm [26].

Persons are not eligible to participate if they have previously been beneficiaries of a previous similar intervention, cannot adequately participate in the intervention actions proposed in the study site (e.g. intellectual disabilities, severe language limitations) or are illegally connected to the electricity grid.

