#### Additional measures

City-level data on air quality, weather, climate, green spaces, and pollution are collected through available open data.

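### If a site enrols its two arms in different months, between-arm change at 6 and 18 months is open to seasonal bias; 12-month change is not

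*Protocol article*

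**What the plan says.** The Study design section of the protocol article sets one schedule for both arms: "Measures are taken at baseline (T0), at 6 months (T1), at 12 months (T2) and 18 months after baseline (follow-up; T3"). It gives a single start for the whole study, "Recruitment of study participants and baseline data collection is scheduled to commence in autumn 2022", with no end date and no timing by arm. According to the abstract, participants are recruited "to receive the WELLBASED intervention programme for 12 months", so T2 is the end of the programme and T3 is the only visit after it.

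On how the arms are formed, the section on study population and eligibility says: "Study sites might apply randomization at individual or cluster level to create intervention and control condition". The Study design section adds: "Potential participants in the catchment area of an intervention or control site receive information about the study". Arms drawn from different areas are therefore possible.

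The intended comparison is between arms. The Objectives section says that "The short, and mid-term effects of the programme on energy poverty and health and wellbeing indicators are evaluated in comparison to a control condition", and the Hypothesis section is worded in the same way.

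On season, the Additional measures section says: "City-level data on air quality, weather, climate, green spaces, and pollution are collected through available open data". It gives no analytic use for these data. The section on data management and analysis describes multilevel regression across the four time points and names no term for season or calendar month. The Limitations section relies on the questionnaire for confounders.

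**The concern.** The protocol itself gives reasons to expect seasonal outcomes. Its Background links cold homes to poorer mental health, to cardiovascular and respiratory disease, and to colds and flu. The energy outcomes include being unable to heat the home, energy consumption and energy spending.

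Six-month steps place T1 and T3 at the opposite point of the year from T0 and T2. If one arm of a site is recruited later than the other, the arms are measured in different months at every visit. The seasonal gap between them at T0 then changes sign at T1 and T3, so subtracting baseline doubles it instead of removing it. The main outcome is change in health-related quality of life, and the power statement is for the 18-month follow-up, which is one of the two exposed visits.

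A second, separate matter remains even when the arms enrol together. If the programme works better in one season than in the other, the arm contrast at T3 can differ from that at T2 for reasons unrelated to the programme having stopped.

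**Working it through.** **The plan's own figure.** Inputs from the Power consideration section: 700 per arm at 18 months, average cluster size 117, intra-class correlation 0.02, alpha 0.05 (taken as two-sided), power 0.80.

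- Design effect: 1 + (117 − 1) × 0.02 = 3.32.
- Effective size per arm: 700 / 3.32 = 210.8.
- Detectable difference: (1.960 + 0.842) × √(2 / 210.8) = 0.273 SD. Power at 0.28 SD is 0.82.

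The stated 0.28 SD is reproduced, slightly on the cautious side, and is used below as the yardstick.

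**Seasonal model (assumed).** S(t) = A·cos(2πt/12), with t in months from a mid-January peak. The amplitude A is not in the documents; 0.05 and 0.10 SD are taken as a range. L is the number of months by which one arm of a site enrols later than the other.

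**Between-arm bias.**

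1. The seasonal gap between arms at T0 is S(t + L) − S(t). Its largest absolute value over all enrolment months is 2A·sin(πL/12).
2. Six or 18 months later the cosine has changed sign, so the gap is the same size and reversed. Twelve months later it is unchanged.
3. The bias in the between-arm difference in change is therefore at most 4A·sin(πL/12) at T1 and at T3, and 0 at T2.

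| Offset L | Worst case, A = 0.05 | Worst case, A = 0.10 | First arm in mid-October, A = 0.10 |
|---|---|---|---|
| 0 months | 0 | 0 | 0 |
| 1 month | 0.05 | 0.10 | 0.10 |
| 2 months | 0.10 | 0.20 | 0.17 |
| 3 months | 0.14 | 0.28 | 0.20 |

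All entries are absolute values in SD. As an example, at A = 0.10 and L = 3 the worst case is 4 × 0.10 × sin(45°) = 0.283. With the first arm in mid-October, S is 0 for that arm and 0.10 for the arm enrolled in mid-January. The gap goes from 0.10 to −0.10, a shift of 0.20.

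**Dilution by pooling.** These figures suppose that every site has the same offset in the same direction. If two of six equally weighted sites had it, the pooled worst case would be 0.283 × 2/6 = 0.09 SD. The site-specific analyses, which the protocol also plans, would not be diluted.

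**T2 against T3 with aligned arms.** The control arm removes a shared seasonal swing but not a seasonal difference in effect. As an assumed illustration, a stable effect of 0.30 SD in one season and 0.15 SD in the other would appear as a halving or a doubling between T2 and T3.

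**The case against.** The strongest reply is that this is a controlled comparison. Both arms follow the same visits, and the hypothesis concerns results "in comparison to the people participating in the control condition". A seasonal swing shared by the arms cancels in that contrast at each visit. Bias needs an enrolment offset, and the protocol permits one without saying that it will occur. Sites that randomise individuals after enrolment have no systematic offset. This stands, and it rules out the stronger reading that a reader might draw from the calendar alone, namely that the 6- and 18-month results are confounded with season.

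Three further replies also stand.

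- The amplitude is assumed. The 0.28 SD figure needs the higher amplitude, a three-month offset, the least favourable enrolment months and the same direction at every site. Autumn and spring may also be alike in temperature.
- No section names the step from T2 to T3 as the measure of persistence. The mid-term objective is answered by the arm contrast at T3, so it would be wrong to say that it cannot be answered.
- It is tempting to treat 18 months as the most exposed visit because the power statement refers to it. By the formula, T1 and T3 are exposed equally.

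A last reply is that recruitment pacing and covariates may be settled in a fuller protocol or an analysis plan that is not shown. For the covariate this is fair. It has less force for enrolment timing, because the article itself sets the visit spacing and makes randomisation optional, and timing cannot be repaired once recruitment is over.

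**Conclusion.** The point holds as a conditional risk. The half-year phase shift follows from the stated schedule. Between-arm change at 6 and 18 months is open to seasonal bias where the arms of a site enrol in different months, and nothing in the article prevents this. For an assumed amplitude of 0.05 to 0.10 SD and an offset of 1 to 3 months, the worst case runs from 0.05 to 0.28 SD. Its upper end equals the difference that the trial is powered to detect. The bias is zero when enrolment is aligned, and zero for 12-month change in any case. The documents do not show that an offset will occur or how many sites would be affected.

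Separately, a difference between the T2 and T3 contrasts cannot tell waning after the programme from a seasonal difference in effect. That limits interpretation and does not invalidate either contrast.

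**What to change.** 1. **Study design section.** Require each site to enrol intervention and control participants over the same calendar months. This is the main safeguard.
2. **Data management and analysis section.** Add calendar month of measurement, or outdoor temperature from the city data, to the multilevel model as a main effect. This supports step 1 but does not replace it. If each arm of a site enrols in one short and separate period, month can hardly be told apart from the arm-by-visit terms.
3. **Reporting.** Give the arm contrast at each visit. State that a difference between the T2 and T3 contrasts mixes waning with any seasonal difference in effect. T3 against T1 matches season and may be shown as a supplement only, because T1 falls halfway through the programme.

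A month-by-arm interaction is not recommended as a way to separate season from waning. Under tight enrolment it is nearly collinear with the visit-by-arm terms.

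The cost is that sites must pace the two arms together and the model spends a few degrees of freedom. The weather data are already to be collected.

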### Intervention condition

Participants in the intervention condition receive the WELLBASED intervention programme. The definition of the WELLBASED urban programme follows the theoretical basis of the social-ecological model [24]. This is characterized by fixed factors (core non-modifiable factors), such as age, sex and genetics, and by a set of potentially modifiable factors expressed as a series of layers of influence. The latter includes personal lifestyle, the physical and social environment and wider socio-economic, cultural and environment conditions. The social-ecological model maps the interactions between the individual, the community, and the physical, social, and political environments that affect health and wellbeing.

A general framework of the urban programme is established and adapted to each study site. Focus groups are implemented in each study site with stakeholders and end-users to co-create the interventions, to ensure that they are carried out according to the real needs of end-users.

Actions are defined for each layer of the social-ecological model, to maximize the scope and benefits of the intervention (please see Additional file 1 for examples of potential actions for each layer in more detail):Individual lifestyle factors: practices oriented to improve individual lifestyles regarding health, energy efficiency, energy costs, and residential comfort (e.g., individual energy advice).Social and community networks: activities oriented to strengthen communities, mainly those oriented to promote community support and mutual aid, and therefore moving from an individual to a collective support approach (e.g., energy cafes).Living and working conditions: practices oriented to improve the access to dignified living conditions, supporting comfortable and healthy homes (e.g., fuel debts support, improved energy efficiency).General socio-economic, cultural and environmental conditions: practices and policies that aim to make structural changes on the socio-economic context, mainly referring to both energy and to household policies (e.g. observatories).

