### Control condition

In the control condition the usual activities of participants continue. No intervention actions are undertaken. Some study sites use a waitlist design to allow participants in the control condition to receive the intervention programme after data collection has terminated. Study sites might provide incentives to control participants such as money, groceries, keeping of study devices after completion of the data collection.

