**ENERGY EFFICIENCY EVALUATION**			
**Energy consumption**	On grid (e.g. electricity, gas, heat) and off-grid (e.g. bottled gas, coal) energy consumption	Online/offline self-reported questionnaire, if possible, smart meters or energy provider	Baseline, 6, 12 and 18 months
**Household income spent on different sources of energy**	% of income/Euros	Online/offline self-reported questionnaire and, if possible, energy provider	

The main outcome is the change in health-related quality of life (HrQoL). This is measured by the EuroQol 5-level EQ-5D (EQ-5D-5L) instrument [27]. Secondary outcome measures include satisfaction with life, mental health, outcomes related to lifestyle behaviour, comorbidities, loneliness, subjective comfort in households, control over life, and social support. Frailty is assessed in older adults. Energy-related outcome measures are energy poverty indicators as defined by EPOV [26], attitudes towards adoption of energy efficiency measures, and coping behaviours.

Additional data on health care use are collected through electronic health records (when possible) for both intervention and control condition. This entails visits to the emergency ward and relevant care use outcomes. If data is not available through the electronic health records this information is obtained in the self-reported questionnaire.

Household spending on energy and energy consumption is obtained for participants in the intervention and control condition via the self-reported questionnaire. Depending on the study site additional data may be collected via smart energy meters or via energy providers.

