#### Data collection in intervention condition

In the intervention condition, additional data will be collected through health monitoring. Peak flow, oxygen saturation (SpO_2_), blood pressure and heart rate are measured every month through the use of health monitoring devices. Devices, such as Fitbit-like trackers, send health data to the data platform directly. In other instances, data is obtained manually during a home visit. Peak flow and SpO_2_ are measured in a resting position and after a six minutes’ walk. Blood pressure and heart rate are measured three times in a resting position with a three-minutes interval. Sleep quality is measured with the Pittsburgh Sleep Quality Index with a three-month interval [38].

Home sensors collect household data on temperature, humidity, and air quality in the intervention condition. Data are collected near real-time.

Qualitative interviews are conducted in each study site with 20 subjects of the intervention to evaluate the impacts of the intervention and to help explain findings. The qualitative research is longitudinal: the first interview takes place after the project has started, and the second when the project is finished. Participants are asked in the baseline questionnaire if they are willing to be involved in the qualitative part of the study. From these volunteers, the baseline questionnaire results are used to construct a sample which reflects the diversity of the main groups identified. Specific attention is paid to ensuring a gender-balanced sample, and to including people who report a range of health and energy poverty experiences. General guidelines for the set-up of the interviews are designed collaboratively across the research team, and training and support in implementation is offered by the lead qualitative partner. Study partners conduct interviews in their study sites and collect qualitative data from the studys’ participants following a consistent but adaptable methodology. Key topics in interviews include the participant’s experience of their home and energy use in the home, their coping strategies in the home, the wider effects of energy poverty and the impacts of the intervention.

Instruments and variables collected in the intervention condition are presented in Table 3.

**Table 3 Tab3:** Instruments and variables collected in intervention arm

Variable	Instrument/indicator	Data source	Timeline

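### Energy spending and consumption rest on unblinded self-report, and only one arm gets energy advice, so part of an arm difference can be a change in reporting

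*Protocol article*

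**What the plan says.** Four statements in the Protocol article bear on this point.

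- **What the intervention arm receives** (Intervention condition): "practices oriented to improve individual lifestyles regarding health, energy efficiency, energy costs, and residential comfort (e.g., individual energy advice"). Other layers include help with fuel debts and better energy efficiency of the home.
- **What the control arm receives** (Control condition): "In the control condition the usual activities of participants continue. No intervention actions are undertaken".
- **How energy outcomes are measured** (Data collection in both study arms): "Household spending on energy and energy consumption is obtained for participants in the intervention and control condition via the self-reported questionnaire". The time points are baseline, 6, 12 and 18 months. On objective data the text says: "Depending on the study site additional data may be collected via smart energy meters or via energy providers". The consumption row of Table 2 gives the source as "Online/offline self-reported questionnaire, if possible, smart meters or energy provider", and the spending row likewise names the energy provider only where possible. The title of Table 2 covers both arms.
- **Blinding** (Study design): "Study participants, intervention providers and research assistants are not blinded due to the nature of the intervention".

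The intervention arm also has home sensors, but these record other quantities: "Home sensors collect household data on temperature, humidity, and air quality in the intervention condition". They cannot check reported energy use. The Limitations section names recruitment and confounding, not reporting.

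**The concern.** Unblinded self-report is common in trials of this kind. Here the intervention also concerns the quantity being reported: a person advised on energy costs may come to know, estimate or present those costs differently. If so, the reporting error moves between T0 and the follow-up visits in one arm and stays put in the other.

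The stake is the energy half of the trial's aim. The Hypothesis section puts energy poverty alongside health and wellbeing. Two of the four EPOV indicators listed under eligibility, which the article also names as outcomes, are cut-offs on expenditure: spending below half the national median, and a share of income above twice the national median share. A reporting shift can carry households across either cut-off. It can do so in opposite directions: lower reported spending moves a household towards the first criterion and away from the second.

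**Working it through.** **1. Why T0 does not protect.** Write reported log spending as true log spending plus an error e that depends on arm (I, C) and time. The arm difference in change from T0 is

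true effect + [(e_I,after − e_I,T0) − (e_C,after − e_C,T0)].

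An error that is constant over time cancels, even if the arms differ. An error that changes in both arms alike also cancels. An error that changes in the intervention arm only stays in full. None of the terms in brackets depends on sample size. Randomisation, where a site uses it, balances the errors at T0 but not those that arise afterwards.

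**2. The plan's own benchmark.** Inputs from Power consideration: 700 per arm at follow-up, average cluster size 117, ICC 0.02, alpha 0.05 (two-sided assumed), power 0.80.

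- Design effect: 1 + (117 − 1) × 0.02 = 3.32.
- Effective number per arm: 700 / 3.32 = 210.8.
- Standard error in SD units: √(2 / 210.8) = 0.0974.
- Detectable difference: (1.960 + 0.842) × 0.0974 = 0.273 SD. Power at the stated 0.28 SD is 0.82.

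The stated 0.28 SD is reproduced closely and is not in dispute.

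**3. How large a shift could be (assumed inputs).** Suppose unaided reports are off by a fraction b in one direction in both arms at T0, and the error vanishes after advice in the intervention arm only. The spurious difference is |ln(1 ± b)| / SD of log spending. The document gives neither b nor the SD. With an assumed SD of 0.4 to 0.6:

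| b | Smallest, SD 0.6 | Largest, SD 0.4 |
|---|---|---|
| 5% | 0.0488 / 0.6 = 0.08 | 0.0513 / 0.4 = 0.13 |
| 10% | 0.0953 / 0.6 = 0.16 | 0.1054 / 0.4 = 0.26 |
| 20% | 0.1823 / 0.6 = 0.30 | 0.2231 / 0.4 = 0.56 |

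With an SD of 0.8 to 1.0, equally an assumption, b = 10% gives 0.0953 / 1.0 = 0.10 to 0.1054 / 0.8 = 0.13. Errors that average zero on this scale give no mean shift at all.

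**4. What a shift would do to the test.** With no true change in energy use and the standard error of step 2 (which carries the plan's ICC over to the energy outcomes), the probability of a significant result is:

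| Assumed shift (SD) | Probability |
|---|---|
| 0 | 0.05 |
| 0.05 | 0.08 |
| 0.10 | 0.18 |
| 0.20 | 0.54 |
| 0.28 | 0.82 |

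With no clustering (700 per arm), shifts of 0.10 and 0.20 SD give 0.47 and 0.96. More precision makes the false finding likelier.

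**5. What meter data could do.** If a share s of participants is analysed on self-report and the rest on objective readings, the average shift is s times as large. With s = 0.5, a shift of 0.20 SD becomes 0.10 SD and the probability falls from 0.54 to 0.18. The article does not fix s.

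**The case against.** The strongest reply is that self-reported describes who completes the form, not how the figure is found. The questionnaire items are not shown, so both arms may already be asked to copy figures from a bill. A reader might infer that controls go on guessing from memory while advised participants learn to read bills and meters. The article says neither: it gives individual energy advice only as an example, adapts actions to each site, and leaves the details to an additional file. That part of the reply stands, so the shift is a possibility and not an established fact.

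Second, Table 2 already lists meter and provider data under a title that covers both arms. This also stands, and it softens the point at sites that obtain such data. It does not remove it, because the data depend on the site and are described as additional to self-report.

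Third, the sizes above rest wholly on an assumed one-directional error that vanishes in one arm. That is right. They show what could happen, not what is likely.

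Fourth, the programme may truly change use and spending, through better energy efficiency or debt support. Agreed. The difficulty is that self-report alone cannot separate a true change from a reporting change.

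A reply that the analysis plan will settle this does not succeed for the data source. No later analysis can recover bill or meter figures that were not collected.

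**Conclusion.** The point holds as a risk to the energy outcomes. Three stated facts support it: energy advice goes to one arm, nobody is blinded, and self-report is the only energy source assured at all sites. Part of an arm difference in energy spending, energy consumption and the two expenditure-based EPOV indicators can therefore reflect reporting that changed after T0.

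Size and direction are unknown. Under the assumptions shown, a shift of 0.08 to 0.56 SD is possible for errors of 5% to 20%, against a planned detectable difference of 0.28 SD, and no mean shift arises if errors average zero.

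A reader might go further and conclude that any energy effect will be a reporting artefact, or that the trial's main result is compromised. The document supports neither. True changes are plausible, some sites may have objective data, and EQ-5D-5L does not depend on reported energy figures. Nor do the other two EPOV indicators, arrears and inability to keep the home warm, depend on reported expenditure. The change is worth making, but the point does not undermine the primary comparison.

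**What to change.** Revise Table 2 and the accompanying text on energy spending and consumption as follows.

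- Have the questionnaire ask both arms, at T0, T1, T2 and T3, for the amount, quantity and dates on the latest bill, meter or receipt (receipts for bottled gas and coal), and mark each value as documented or recalled.
- Where a site can obtain meter or provider data, collect them in the same way in both arms and use them in place of self-report for that site's energy comparison.
- Keep all participants in the main intention-to-treat comparison. Report the share of documented values by arm and time point.
- Run the comparison restricted to documented values as a sensitivity analysis only. Making it the main analysis would select on something measured after baseline that the advice may itself change, since advised participants may more often have a bill to hand.
- Name differential reporting in the Limitations section.

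The cost is a few extra questionnaire fields, a few minutes per visit and one sensitivity analysis. Some values will still be recalled, so the risk is reduced and made visible rather than removed.
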